## Abstract

**Background:**

Tuberculosis is a public health problem in Cameroon, just like in many other countries in the world. The National Tuberculosis Control Programme (PNLT) put in place by the state, aims to fight tuberculosis through the implementation of international directives (Directly Observed Treatment Short, DOTS). Despite the deployment of this strategy across the world, its implementation is difficult in the context of low-resource countries. Some expected results are not achieved. In Cameroon, the cure rate for patients with sputum positive pulmonary tuberculosis (TPM+) after 6 months is only about 65%, 20% below the target. This is mainly due to poor patient adherence to treatment. By relying on the potential of mobile Health, the objective of this study is to evaluate the effect of SMS reminders on the cure rate of TPM + patients, measured using 6-month bacilloscopy.

**Methods/design:**

This is a blinded, randomised controlled multicentre study carried out in Cameroon. The research hypothesis is that sending daily SMS messages to remind patients to take their prescribed tuberculosis medication, together with the standard DOTS strategy, will increase the cure rate from 65% (control group: DOTS, no SMS intervention) to 85% (intervention group: DOTS, with SMS intervention) in a group of new TPM + patients. In accordance with each treatment centre, the participants will be randomly allocated into the two groups using a computer program: the intervention group and the control group. A member of the research team will send daily SMS messages. Study data will be collected by health professionals involved in the care of patients. Data analysis will be done by the intention-to-treat method.

**Discussion:**

The achieving of expected outcomes by the PNLT through implementation of DOTS requires several challenges. Although it has been demonstrated that the DOTS strategy is effective in the fight against tuberculosis, its application remains difficult in developing countries. This study explores the potential of mHealth to support DOTS strategy. It will gather new evidence on the effectiveness of mHealth-based interventions and SMS reminders in the improvement of treatment adherence and the cure rate of tuberculosis patients, especially in a low-resource country such as Cameroon.

**Trial registration:**

The trial is registered on the Pan-African Clinical Trials Registry (http://www.pactr.org) under unique identification number: PACTR201307000583416.

## Background

As in many other countries in the world, tuberculosis is a major public health problem in Cameroon. In 2010, there were 24,528 cases of tuberculosis (all forms included) with a prevalence rate of 122 per 100,000 inhabitants [1]. The number of new sputum positive cases in the country was 14,464 in 2010 [1]. With an estimated HIV prevalence rate of 5.3% [2], the rate of co-infection was estimated at 33% in new cases of sputum positive pulmonary tuberculosis (TPM+) [1].

In accordance with international directives (Directly Observed Treatment Short, DOTS [3] and the Global Strategy and Plan to Stop TB [4,5]), Cameroon has established the National Tuberculosis Control Programme (PNLT) for the fight against tuberculosis, financed by the state and international funding partners such as the Global Fund. This national programme aims to elaborate on and execute the National Policy in the fight against tuberculosis [1]. However, the DOTS strategy is often not well applied because its implementation, especially in developing countries, is complex [6], has numerous barriers [7] and needs enormous resources [8]. This is why there are many adaptations (Partially Observed) depending on the context. In the treatment of tuberculosis in Cameroon, for instance, during the intensive phase of treatment (the first two months), instead of receiving daily observable drug doses, a patient receives several doses weekly or monthly. In the continuation phase (from the third to the six month) they receive these doses monthly.

Irregular adherence to tuberculosis treatment causes therapeutic failure, leads to prolonged periods of infectiousness [9], provokes relapses [10], favours the emergence of drug resistance [11,12], requires prolonged and expensive treatment schemes, which do not guarantee effectiveness [13], and finally, increases morbidity and mortality [9].

The therapeutic success rate is the proportion of cases that complete 6 months of treatment and where a sputum test carried out at 5 months finds no Koch’s bacilli (KB). The cure rate is the proportion of cases that complete 6 months of treatment and where a sputum test carried out at 6 months finds no KB. In Cameroon, the therapeutic success rate is around 77% [2], while the cure rate is around 65% [2], which is 20% below the objective fixed by the PNLT. This low cure rate may be due to several causes.

It has been shown that the cure rate for tuberculosis is related to adherence to tuberculosis treatment and inversely related to HIV prevalence in the population, and to the prevalence of multi- or ultra-treatment-resistant cases [14]. According to actors in the field, one of the main causes of the low cure rate in Cameroon is non-adherence to treatment by tuberculosis patients. Also, according to these local actors, this failure in adherence itself could be due to a lack of communication and interactions between health staff and patients during the care process.

There has been a continuous expansion of mobile technologies across the world (for example, 95% of the world’s people are expected to have a mobile telephone by 2014), including developing countries. The increased use of mobile technology, such as the Short Message Service (SMS), has significant potential for health systems, and is termed mobile health (mHealth) [15,16]. SMS-based interventions involving health staff and patients can contribute to the improvement of health process and clinical outcomes [17,18]. The interventions are cost-effective both in urban and rural settings [19]. Many studies have explored the potential of mHealth (such as SMS reminders) for health objectives in the antiretroviral treatment of HIV [20-24]. Some of these interventions have been effective in improving adherence to antiretroviral treatment [23,24] and reducing viral load [23]. Effects have been observed in the prevention of HIV transmission from mother to child [25] on the adherence of health staff to guidelines for the management of malaria [26,27] and its control [28], and for the management of drug stocks [29].

For tuberculosis, studies have shown the utility of mobile phones. For example, they can be used to transmit laboratory images and results to improve notification and to reduce delays in the management of tuberculosis [30]. They can be used in the care of distant patients, as well as in the training of health staff [31]. Quite a number of studies have explored the possibility of using SMS to improve adherence to tuberculosis treatment [16,32] but none to date have looked the effect of the cure rate.

The aim of this study is to explore the potential of SMS-based reminders to improve adherence to tuberculosis treatment and to increase the cure rate in Cameroon, where adherence remains suboptimal because of a non-exhaustive implementation of DOTS.

## Methods/design

### Primary objective

The primary objective of this study is to evaluate the effect of daily SMS reminders on the cure rate of TPM + patients.

### Primary research hypothesis

Our primary hypothesis is that sending daily SMS messages to remind patients to take their prescribed tuberculosis medication, together with DOTS, will increases the cure rate (defined as the absence of KB in the sputum in a control test carried out at 6 months) from 65% (DOTS, no SMS intervention) to 85% (DOTS, with SMS intervention) in a group of adult patients newly diagnosed with TPM + in Cameroon.

### Secondary objectives

The secondary objectives of this study are to evaluate the effect of sending SMS reminders on:

•Patient adherence to tuberculosis treatment (drug prescriptions collected and doses taken).

•The punctuality of appointments during the second, fifth and sixth months as well as whether appointments were kept.

•The number of treatment failures (KB positive patients at 5 months).

•The number of participants who develop resistance (as measured by Genexpert [33]).

•The degree of satisfaction of the participants.

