### Cure status

A participant is considered to be:

•Cured, if they have a negative smear test after 6 months of treatment.

•Not cured or a treatment failure if they have a positive smear test after 5 months of treatment.

•Transferred, if they are referred to continue treatment in another Treatment and Diagnostic Centre out of the study zone.

•Dead, if they die between the screening phase and the end of treatment, regardless of the cause of death.

•Lost to follow-up, if they receive at least one month of treatment and are not in any of the classes above.

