**Primary**			
**Cure**	**Percentage of cured patients**		
Bacilloscopy (second, fifth, sixth months)	Percentage of patients with positive or negative bacilloscopy results	Categorical	Chi-square
Cure (sixth month)	Percentage of cured patients	Binary	Chi-square
			Logistic regression

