**Secondary**			
**Adherence of patients to treatment (second, fifth, sixth months)**			
Drug prescriptions collected and doses taken (visual analogue scale)	Percentage of adherence to treatment during the last 30 days	Continuous	*t*-test
Keeping appointments		Binary	Chi-square
Punctuality of appointments		Categorical	Chi-square
**Multi-drug-resistant tuberculosis (fifth and sixth months)**	Percentage of patients with multi-drug-resistant tuberculosis	Binary	Chi-square
**Satisfaction (sixth month)**	Satisfaction	Continuous	*t*-test

The status of each patient will be based on the results of smear tests carried out in the second, fifth and sixth months in the treatment centre. At the fifth month, two scenarios are possible. If the smear test is negative, treatment continues during the sixth month. At 6 months, the final smear test is done to see if the patient is cured. If this test is negative, the patient is classified as cured.

If the test at 5 months is positive, a second smear test will be performed to confirm the result (which is not mandatory for this study). At this moment, the patient will be considered as a treatment failure and classified as not cured in the study.

Participants lost to follow-up or referred to other treatment centres, will be considered cured (best case) or not cured (worse case) as two extreme statistical scenarios.

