### Sample size

Presently, the cure rate for tuberculosis with the DOTS strategy is around 65% [2] in Cameroon, about 20% lower than the objective fixed by PNLT. Our hypothesis is that the cure rate in the SMS intervention group will reach 85%. For an attribution ratio of 1:1 in the two groups, 80% power, an alpha error of 5% and a two-sided test (effects may be interpreted independent of the way they go), we require a sample size of at least 166 participants [39], 83 in the SMS intervention group and 83 in the control group. Considering that the risk of loss to follow-up at the end of the study is important, we increased the sample size by 20%, giving 199 participants. Also, for the urban zone, we estimated that at least 90% of eligible people will have mobile phones and that at least 80% of them will consent to take part. The total number of eligible participants was therefore increased by 10% and another 20%, leading to a total of 260 participants.

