### Plan for data analysis

The results of this study will be reported following CONSORT standards [40] on randomized trials. A data entry mask developed using the Epi Data Entry program by the main investigator will be used to enter and control the quality of patient data. Analysis of the primary outcome will use the intention-to-treat approach, which includes all participants in their initial study group allocation. All participants for which there are no smear test results at 6 months will be considered not cured or cured (worst case or best case scenario). Results will be presented depending on the type of variable: means (± standard deviation) and medians (minimum and maximum) for continuous variables and percentages for categorical or binary variables.

The two groups will be described according to their baseline characteristics. Student’s test (*t*-test) will be used to calculate the difference between the two groups for continuous variables while the chi-square test will be used for categorical or binary variables. The association between study groups and cure rate will be analysed using a logistic regression model reporting the odds ratio and 95% CI.

Each individual characteristic, such as age, sex, level of education, socio-economic category, and HIV status, will be tested for an association with the cure status in a univariate analysis of the control group. Each characteristic that is significantly related with the outcome (*P* < 0.1) will be tested using a bivariate model that includes the study group, cure status and the potential confounder. If introducing the variable changes the odds ratio by more than 10%, then the variable will be considered as a potential confounder of the association and will be used in the final multivariate model.

The data from this study will be analysed using the SPSS programme (v21.0) or STATA (v11). Comparisons between the two groups will be expressed in terms of the odds ratio and the number needed to treat. Open questions in the questionnaire (especially problems observed during follow-up) will be analysed using the content analysis technique.

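### Month-5 treatment failure is a count of positive smears with no place for a missing smear, so it rises with attendance, which the SMS is meant to improve

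*Protocol article*

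**What the plan says.** - **Outcome.** "Secondary objectives" lists "The number of treatment failures (KB positive patients at 5 months" as an outcome, without a denominator.
- **Class.** "Cure status" requires a positive result: "Not cured or a treatment failure if they have a positive smear test after 5 months of treatment". Transferred and dead participants have their own classes. The residual class is "Lost to follow-up, if they receive at least one month of treatment and are not in any of the classes above".
- **Table 1.** The bacilloscopy row covers months 2, 5 and 6, is tested by chi-square, stands under the heading Primary, and is measured as "Percentage of patients with positive or negative bacilloscopy results". It has no entry for a missing smear.
- **Missing smears.** The section Plan for data analysis states: "All participants for which there are no smear test results at 6 months will be considered not cured or cured". The text below Table 1 states: "Participants lost to follow-up or referred to other treatment centres, will be considered cured (best case) or not cured (worse case". Both assign cure status. The same plan section ties the intention-to-treat approach to the primary outcome.
- **Attendance.** "Secondary objectives" also makes keeping the month-2, month-5 and month-6 appointments an outcome that the SMS may change.
- **Loss.** "Sample size" treats loss to follow-up as an important risk and adds 20% for it.

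**The concern.** A participant can be recorded as a month-5 failure only if a smear is taken. Someone who misses the visit adds nothing to the count, and on the text as written has no value in the month-5 row of Table 1. The intervention acts on exactly this step. If reminders bring in more participants at month 5, the SMS arm has more chances to record a positive. The article itself links irregular adherence to therapeutic failure (Background), so those brought in may also be positive more often than regular attenders.

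At stake is the reading of a named secondary outcome. An SMS programme that only improves retention could appear to produce more treatment failures, and a real reduction could be hidden.

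**Working it through.** **Inputs from the article.** 288 participants included ("Trial status"), so about 144 per arm at 1:1. Loss allowance 20% ("Sample size": 166 × 1.2 = 199.2, the stated 199). National therapeutic success about 77% (Background), so about 23% do not reach it. That 23% is not split into failure, loss and death. The article gives no figure for month-5 attendance or positivity, so there is no plan figure to reproduce on this point.

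**Assumptions.** No month-5 smear: Lc = 20% control (the study-end allowance, borrowed for month 5), Ls = 8 to 14% SMS. Positivity r = 3 to 4% in those seen under usual care and l = 10 to 30% in those who would otherwise be lost. The SMS has no effect on positivity.

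**Step 1: equal positivity (l = r).**
- Ratio of counts = (1 − Ls)/(1 − Lc) = 0.92/0.80 = 1.15.
- At 4%: 144 × 0.80 × 0.04 = 4.6 v 144 × 0.92 × 0.04 = 5.3.
- Percentage of those tested: 4.0% v 4.0%, so no bias on that scale.

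**Step 2: extra attenders more often positive.**
- Control count = 144 × (1 − Lc) × r.
- SMS count = 144 × [(1 − Lc) × r + (Lc − Ls) × l].
- Ratio of counts = 1 + (Lc − Ls) × l / [(1 − Lc) × r].

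| r | l | Ls | Ratio of counts |
|---|---|---|---|
| 4% | 10% | 14% | 1 + 0.006/0.032 = 1.19 (minimum) |
| 4% | 20% | 8% | 1 + 0.024/0.032 = 1.75 |
| 3% | 30% | 8% | 1 + 0.036/0.024 = 2.5 (maximum) |

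For the middle row, the counts are 144 × 0.032 = 4.6 v 144 × 0.056 = 8.1. Among those tested this is 4.0% v 0.056/0.92 = 6.1%, a ratio of 1.52.

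**Step 3: chance of a significant result in the wrong direction (middle row, normal approximation).**
- Among those tested: difference 0.0209, standard error about 0.028, chance about 11%.
- Over all randomised: difference 0.024, standard error about 0.024, chance about 17%.

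**Step 4: a true 30% reduction in positivity in the SMS arm (Ls = 8%, r = 4%).**
- l = 20%: 0.7 × 8.06 = 5.6 v 4.6 failures, or 4.3% v 4.0% of those tested.
- l = 10%: 0.7 × 144 × 0.044 = 4.4 v 4.6, so no reversal.

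**Step 5: what the existing best/worst-case device would show at month 5 (middle row, no SMS effect).**
- No smear counted as not a failure: 4.6 v 8.1 of 144.
- No smear counted as failure: 144 × (0.20 + 0.032) = 33.4 (23.2%) v 144 × (0.08 + 0.056) = 19.6 (13.6%).

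The two extremes point in opposite directions, which the count of positives alone does not reveal.

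**The case against.** The strongest reply is that this is detail that an article leaves to the full protocol or analysis plan: denominators and missing data for one secondary outcome. That would dispose of a complaint of mere silence. It does not dispose of this one, because the outcome itself is fixed as a number of positives and the failure class requires a positive smear.

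Other objections stand in part:

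- **Classes already exist.** Dead, transferred and lost participants are named under "Cure status". The participant with no class of this kind is the one still in care who gives no month-5 sputum. But none of these classes is carried into the month-5 comparison.
- **Intention to treat may reach the smear rows.** Table 1 places bacilloscopy under Primary, so the all-participants approach can be read as covering it. Even so, the sentence on missing smears names month 6 only and gives no smear value.
- **Best/worst case may reach failure.** "Cure status" pairs not cured with treatment failure, so the scenarios could be extended to failure. As written they assign cure status, and they do not cover someone who misses month 5 but stays in care.
- **The rates are assumed.** The 20% is an allowance for the end of the study, the SMS-arm loss is invented, and the model supposes that retained patients keep the positivity of those who would have been lost. Staying on treatment may well lower it.

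A reader might infer that the percentages are certainly computed among those tested, or that the comparison is bound to turn against SMS. The article supports neither. It states no denominator, and the tested-only percentage is unbiased when extra attenders are no more often positive.

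**Conclusion.** The point holds in a limited form. As fixed, the count of month-5 failures depends on attendance, which the intervention is meant to change. With equal positivity and 80% v 92% seen, the false ratio is 1.15. With more positives among the extra attenders it is about 1.19 to 2.5 under the stated assumptions. The percentage among those tested is distorted only in the latter case.

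Expected counts are small, so the main danger is a misleading direction, not a reliably significant false result (about 11 to 17% in the middle case). It would be too strong to say that a true benefit will be reversed: under a 30% reduction the reversal is about one event, and it disappears when positivity in those otherwise lost is 10%. The 6-month cure comparison has its own rule for missing smears and is not affected.

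**What to change.** 1. In Table 1 and the section Plan for data analysis, analyse month-2 and month-5 smear status in all randomised participants by arm with three levels: negative, positive, no smear. Break the last level down into dead, transferred, lost, and in care without sputum. The chi-square already planned can be used.
2. Extend the existing best/worst-case handling to month-5 failure, covering every participant without a month-5 smear.
3. State that the count of positives alone will not be interpreted as an effect on failure.
4. Optionally add a documented negative smear at month 5, over all randomised, as a supporting comparison only. It mixes attendance with bacteriological response and favours the arm with better attendance. In the middle case it would be 0.80 × 0.96 = 76.8% v 0.92 − 0.056 = 86.4% with no effect on positivity.

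The cost is wording, one more table level and one sensitivity analysis. No new data are needed. The downside is a less clean comparison of failure.

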### Study design

This is a blinded, randomised controlled multicentre study. Patients meeting the inclusion criteria will be recruited and randomised by centre into two groups (ratio 1:1): an intervention group in which participants receive SMS reminders in addition to the usual DOTS programme versus a control group where participants follow only the usual DOTS programme (Figure 1).

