### Participants and inclusion and exclusion criteria

Participants eligible for this study must be newly diagnosed with TPM + and aged at least 18 years (born before 1 January 1995). The usual diagnostic procedure of the PNLT will be followed, which is that all patients with clinical signs of pulmonary tuberculosis will undergo two smear tests in the laboratory selected for the study. At least one of these tests must be positive. In addition, the patient must know how to read French or English, have a mobile phone for personal use, know how to open and read an SMS on a telephone and give consent (signed on the informed consent form) after having been informed about the goals, the process and the expected results of the study. Hospitalised patients or severely ill patients, as identified by health staff, will be excluded.

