#### Intervention group

The participants in the intervention group (SMS intervention) will receive daily SMS reminders in French or English. These messages will aim at reminding, inciting or motivating them to take their prescribed tuberculosis drugs. To maintain their attention and interest, these messages will be changed every two weeks (for example, ‘Good morning, it is important to take your drugs against TB every day’ , ‘Good morning, taking drugs daily increases your chance of healing’ , and so on). Additional encouraging messages will also be sent every 2 weeks (for example, ‘Congratulations! The first month of treatment is over’ , and so on). Messages are neutral and similar for both sexes. During each clinical follow-up (a visit at health centre), problems (such as side effects of drugs, problems with adherence to treatment and SMS reception) as well as solutions will be recorded by health staff in the participant’s health records and by the secretary in the daily log. Participants will also receive messages at the end of treatment to thank them for participating in the study.

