#### Control group

Participants in the control group will only receive a welcome message at the beginning, to validate their entry into the study, and a message at the end of treatment to thank them for their participation. These participants will not receive daily SMS reminders.

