### Randomisation

In the first step, participants will be stratified according to recruitment centre. The different treatment centres will be alphabetically coded (A, B, C and so on) and participants attached to each centre will be given numerical codes (for example, patients in centre A will be numbered A001, A002 and so on).

Randomisation will be carried out using a computer program by the main investigator. Participants who are eligible and who have consented to participate in the study will be registered. Their study identifier and telephone number will be communicated to the main investigator and to the secretary, for their randomly allocation by centre into one of the two groups (intervention or control) and for the continuous updating of the mailing of SMS respectively.

The health staff in the hospitals will not be involved in the allocation of participants into groups. This prevents allocation bias and minimises the risk of selection bias (simple blind).

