### Data collection

Health staff taking care of participants in the study will collect data using patient follow-up files developed by the research team. These will contain all the necessary questionnaires, scales and lists of problems. The follow-up files will be kept with the participants’ health records. A marker will be placed on the file of each participant to reduce the risk of them being ‘forgotten’ by health staff during the study. Forms in the file will be completed in French for each visit (the day of inclusion and the second, fifth and sixth months).

Before the onset of recruitment, a meeting will be held with the staff members of the treatment centres. This will inform them of and validate the strategies for the implementation of the study (inclusion of participants, collection of data, use of VAS by patients to evaluate adherence, transmission of data and so on).

During the recruitment phase, a secretary will be responsible for collecting telephone numbers from the participant study files twice a week from each Treatment and Diagnostic Centre. These will be entered into the SMS database. The secretary will also collect socio-demographic data (from the day of inclusion), smear test results (from the day of inclusion, and the second, fifth and sixth months), punctuality data and results of resistance to rifampicin tests (Genexpert).

At least two sessions to supervise staff members (2 months and 6 months after the onset of recruitment) will be carried out in each centre so that data collection remains effective and consistent. Treatment centres facing problems will receive additional training and supervision at appropriate intervals. After recruitment, the secretary will collect data once a week to keep statistics and participant registers up to date. At the final follow-up (during the third visit at the end of the sixth month), health staff will administer a self-evaluation questionnaire on the degree of satisfaction to the participants.

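### The trial is called blinded, but the plan supports only allocation concealment; VAS adherence and satisfaction are at risk of bias, and it is unclear whether problem recording is the same in both arms

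*Protocol article*

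**What the plan says.** The Abstract and the Study design section both use the word blinded: "This is a blinded, randomised controlled multicentre study". Neither says who is blind. The one passage that bears on it is in Randomisation: "The health staff in the hospitals will not be involved in the allocation of participants into groups", followed by "This prevents allocation bias and minimises the risk of selection bias (simple blind").

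On the arms themselves, the Intervention group section says "The participants in the intervention group (SMS intervention) will receive daily SMS reminders in French or English". The Control group section gives that arm a welcome and a closing message only: "These participants will not receive daily SMS reminders". Participants consent "after having been informed about the goals, the process and the expected results of the study" (Participants and inclusion and exclusion criteria).

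On who records what:

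- **Visits.** Under Intervention group, drug side effects, "problems with adherence to treatment and SMS reception) as well as solutions will be recorded by health staff" in the health record, and by the secretary in a daily log.
- **Adherence and satisfaction.** Under Secondary outcomes and Data collection, the health staff who follow the patients record the self-rated VAS at months 2, 5 and 6, and administer the satisfaction questionnaire at month 6.
- **Secretary.** Under Randomisation, the secretary receives study identifiers and telephone numbers to keep the SMS mailing current. Under Data collection, "The secretary will also collect socio-demographic data (from the day of inclusion), smear test results", together with punctuality data and rifampicin-resistance (Genexpert) results.

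**The concern.** Blinding and allocation concealment guard against different biases. Concealment stops the recruiter from steering patients into an arm. Blinding stops knowledge of the arm from changing care, reporting or assessment after allocation. The Randomisation section claims protection against allocation and selection bias only, so it supports the first property and not the second.

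The outcomes at stake are those that rest on a person's report. Patients in the SMS arm spend six months reading messages that urge daily drug-taking and are then asked, by the staff who treat them, how well they took their drugs. A difference on the VAS could reflect what they feel expected to answer. Satisfaction is collected in the same setting. The article also plans to examine whether good adherence improves cure, so any distortion in the VAS would carry into that analysis.

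A second question concerns what is being compared. If writing down problems and solutions at visits happens only in the SMS arm, and leads to action, that arm receives something besides messages, whereas the primary objective is the effect of the reminders.

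**Working it through.** The plan gives no figure for this point, and the sample size does not bear on it. The check is a comparison of sections.

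**1. Who can know the arm**

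| Person | What the article says | What follows |
|---|---|---|
| Participant | Daily SMS in one arm; welcome and closing message only in the other; consent covers the process of the study | Knows, or can readily work out, the arm |
| Secretary | Keeps the SMS mailing updated, keeps the daily log, collects smear, punctuality and Genexpert results | Holds data that reveal the arm alongside outcome data; no masking step described |
| Treating staff | Take no part in allocation; record SMS-reception problems at visits | Not told the arm, but can infer it: a problem with daily messages can arise only in the arm that gets them |
| Smear readers | Nothing stated | Unknown; an article may leave this to the full protocol |

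No row names a person who is said to remain unaware of the arm until outcomes are recorded.

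**2. Which outcomes are exposed**

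- VAS adherence: rated by a participant who knows the arm, recorded by staff who can infer it. Exposed.
- Satisfaction: same people, same setting. Exposed.
- Adherence against cure: uses the VAS. Exposed through it.
- Smear at months 5 and 6: a laboratory result that the secretary collects after it has been produced. Less exposed.

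**3. Is problem recording the same in both arms?**

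- Intervention group: problems and solutions are recorded at each clinical follow-up. The Control group section has no matching text.
- Implementation of the study: adherence follow-up, education and counselling go to all participants.
- Data collection: the follow-up files of study participants contain problem lists, with no restriction by arm.
- Plan for data analysis: problems observed during follow-up are to be content-analysed, again with no restriction by arm.

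One section points to one arm and three point to both. The text does not settle it.

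**4. How sensitive the VAS comparison is (illustration only)**

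The shift and the standard deviation below are assumptions; neither is in the documents. Patients per arm: 288 included (Trial status), less the 20% allowed for loss (Sample size, read here as 20% lost), halved: 288 × 0.8 / 2 = 115. With no true effect and a reporting shift d in favour of SMS, SE = SD × √(2/115), and the chance of a significant result favouring SMS is about Φ(d/SE − 1.96).

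| SD | d | SE | d/SE | Chance |
|---|---|---|---|---|
| 20 | 2 | 2.64 | 0.76 | 11% |
| 20 | 5 | 2.64 | 1.90 | 47% |
| 30 | 2 | 3.96 | 0.51 | 7% |
| 30 | 5 | 3.96 | 1.26 | 24% |

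The nominal value in that direction is 2.5%. The range from 7% to 47% shows that the answer depends on the assumption chosen. It is not an estimate of bias in this trial.

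**The case against.** Several objections have force.

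- **Staff unblinding is not stated.** The article keeps staff out of allocation and nowhere tells them the arm. SMS reception is listed as an example of a problem that is recorded; the text does not say that staff ask every patient about it. This stands: staff can infer the arm, and no more can be said.
- **The secretary transcribes and does not judge.** Nothing gives the secretary a role in reading smears, and masking of readers may be in the full protocol. This stands, and it is why the primary outcome is only less protected than the label implies.
- **Self-report is declared.** The article openly calls the VAS an indirect, self-evaluated measure, and satisfaction may differ because patients like the messages, which the trial sets out to measure. A difference is therefore not proof of bias. This stands, but it does not make the outcomes blinded.

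A reader might go further and infer that the design adds staff problem-solving to the SMS arm, so that any cure effect is not due to SMS alone. The documents do not support that. The Intervention group section speaks of recording and orders no extra action, and the three sections listed in step 3 suggest that adherence follow-up and problem lists cover both arms. A reader might also infer that the subjective outcomes are biased by a known amount. The documents contain no figure for that.

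What the objections do not remove is the mismatch between the label and the procedures.

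**Conclusion.** The concern holds as a mislabelled design property with a risk-of-bias consequence. What the article offers as blinding is allocation concealment. Participants are open, the secretary handles both the mailing and the outcome data, and treating staff can infer the arm while collecting VAS adherence and satisfaction. Those outcomes and the adherence-cure analysis are at risk of bias; the smear-based primary outcome is less exposed.

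The size of any bias cannot be computed from the documents. The only quantities available rest on an assumed shift of 2 to 5 points and an assumed SD of 20 to 30.

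On co-intervention, the finding is an ambiguity: the sections on implementation, the intervention group, data collection and data analysis must be reconciled on whether problem recording, and any action that follows it, is the same in both arms. Unequal handling is possible but not established.

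**What to change.** 1. Replace the word blinded in the Abstract and Study design with open-label for participants. State who, if anyone, is blind, including whether smear readers are. Describe the Randomisation passage as allocation concealment.
2. Keep SMS-reception problems in the secretary's log only, out of the health-staff record. Patients may still mention the messages, so this reduces staff awareness of the arm without removing it.
3. Use one identical problem and solution form in both arms, and say so in both arm descriptions.
4. Take smear results directly from the laboratory record. This limits room for discretion in transcription, but it does not mask a secretary who holds the mailing list by study identifier, even if the results file omits the arm. Full separation would need a second person.
5. Report VAS adherence and satisfaction as unblinded, supportive outcomes, with the same caveat on the adherence-cure analysis.

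The cost is wording, one form and a note to centres; SMS-reception problems would also need a route to the secretary that bypasses clinic staff. The blinded label is lost. Because recruitment has stopped with 288 included, a form change can apply only to remaining visits, and its date should be recorded so that earlier and later data can be told apart. Items 1 and 5 can be made whatever the stage of follow-up.
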